#### Secondary outcomes and mediation

Secondary outcomes will be examined using repeated-measures Analysis of Variance (ANOVA) with further analyses to explore mediation [64,65].

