#### Aims of trial

Within the parameters of phase 2 translational research, the aim of this effectiveness study is to examine the clinical impact and health economics of MBCT where efforts are made to assess for and prevent resentful demoralization and under real-world conditions - within a population representative of the intended target audience, that is, people with a history of depression regardless of their antidepressant regimen. For a long-term preventive intervention evidence of a longer duration of effect would be more desirable than the 12-18 month periods so far examined and 2-year follow-up is planned in this study. The portability of MBCT training has not been assessed and this project will investigate outcomes from a novel training program using instructors who may not have a long-standing and deep knowledge of the intervention provided.

The secondary aim of the project is to provide for a detailed examination of the mechanisms by which this form of therapy may prevent depressive relapse, with this examination structured in a way so as also to progress the understanding of the clinical applicability of MBCT as a treatment for relapse prevention in depression. MBCT may act to reduce relapse through a number of mechanisms outlined in the model shown in Figure 1. According to this model, the two primary mediators for outcome in terms of reduced depressive relapse are 1) increased mindfulness and 2) improved relaxation skills which occur as the result of adopting a meditation practice. We have postulated that these factors may have positive downstream effects on other secondary mediating factors such as rumination, neuroticism, medication adherence and anxiety. Although it will not be practicable to explore validation of this causal nexus fully, we will use it to guide our choice of measures through the research plan that follows.

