### Power analysis

A power analysis was conducted using estimates of annual relapse rates obtained from the literature. Systematic reviews and meta analyses were mainly utilised including: no treatment (or placebo) only [35-38]; psychological treatment alone; effect in recurrent depression of medication alone [35,37,38]; and combined psychological and pharmacotherapy [39,40]. From these sources, anticipated relapse rates over a 2-year period were: no treatment, 56%; MBCT alone, 31%; medication alone, 31%; and MBCT and medication together, 15%. Based on findings from recruitment in our pilot study, we assumed that 70% of the sample would be taking at least some reasonably effective dose of medication, and 30% would not. Applying the subgroup specific odds ratios suggested the following relapse rates as likely over a 26-month period: MBCT group 21.5%; and DRAM group 41.7%. A power analysis showed that to detect this difference using an uncorrected chi-squared statistic at 80% power and α = 0.05 would require a sample size of 82 participants to complete the full 26 months in each of the MBCT and DRAM groups [41]. Further, assuming a dropout rate of 20% led to a recruitment target of 102 participants for each group.

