### Procedure

#### Assessments

Experience from pilot work [62] indicated that the primary reason for exclusion from that study was failure to meet the selection criteria related to MDD. Referrals to the project are therefore screened over the phone using a brief questionnaire based on key questions from the Depression module of the Lifetime version of the CIDI 2.1. Potentially eligible candidates then are invited to complete an intake assessment to assess eligibility and collect baseline data. Following the intake assessment, eligible participants are randomised in cohorts to treatment condition. For participants in both treatment conditions, PHQ assessments are completed at intake and then at monthly intervals from the fourth week of the MBCT program conducted for their cohort. The CIDI 2.1 12 month version, Service Utilization, Hill-Bone Medication Taking Scale, IPPI, CEQ and Beliefs about Relapse are completed at 12 months and 24 months following the conclusion of the MBCT program. The CEQ is also administered at the fourth and eighth week of the MBCT program and Beliefs about Relapse at 8 weeks. The remaining self-report assessments are administered 3 monthly.

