### Statistical analysis

#### Primary outcomes

Intention-to-treat (ITT) analysis will be the primary analytic framework. Groups will be compared using chi-square or Fisher's exact test for proportions and *t*-test or Mann-Whitney-test for continuous variables. Time to relapse/recurrence of depression will be examined using the Kaplan-Meier survival analysis. The Cox proportional hazards regression analysis will be used to examine the effect of covariates such as treatment expectations on time to relapse/recurrence. Per protocol (PP) analyses will also be undertaken. As in previous trials, at least four sessions will be considered as the minimal treatment dose. However, as the MBCT program is sequential and participants are strongly encouraged to attend all sessions, or at least miss no more than one [63], we will also examine outcomes for people who attended the recommended dose of therapy, being 7-8 sessions.

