#### Economic evaluation

The incremental cost of MBCT is the cost of treatment less any savings in health service use. Results of incremental cost-effectiveness analysis will be subject to extensive probabilistic sensitivity analysis [66] using @Risk software, which allows the results to be presented as cost-effectiveness acceptability curves [67]. The cost-utility of MBCT + DRAM compared to DRAM alone will be compared using repeated-measures ANOVAs.

As recommended by Hollis and Campbell [68], sensitivity analyses will be undertaken across these analyses to examine the potential influence of the missing data using various forms of imputation. Where appropriate, given the design of the study, multilevel modelling will be employed [69].

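### The main analysis named for the secondary outcomes and cost-utility, repeated-measures ANOVA, loses participants with incomplete data; the mixed model the article already allows should be named instead

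*Protocol article*

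**What the plan says.** Under Secondary outcomes and mediation, the protocol article gives one sentence of method: "Secondary outcomes will be examined using repeated-measures Analysis of Variance (ANOVA) with further analyses to explore mediation". Under Economic evaluation it adds: "The cost-utility of MBCT + DRAM compared to DRAM alone will be compared using repeated-measures ANOVAs".

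The timing comes from two other sections. Aims of trial says "2-year follow-up is planned in this study". Assessments lists some instruments as annual ("Hill-Bone Medication Taking Scale, IPPI, CEQ and Beliefs about Relapse are completed at 12 months and 24 months") and then says "The remaining self-report assessments are administered 3 monthly". The three-monthly group therefore includes the mindfulness, rumination, anxiety, work-and-social-adjustment and AQoL measures. Service utilisation is also annual.

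Three further statements bear on missing data:

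- Power analysis sets the recruitment target "assuming a dropout rate of 20" per cent, giving 102 per group.
- Primary outcomes says "Intention-to-treat (ITT) analysis will be the primary analytic framework".
- The last paragraph of Economic evaluation says "sensitivity analyses will be undertaken across these analyses to examine the potential influence of the missing data using various forms of imputation", and then allows multilevel modelling if the design makes it appropriate. It does not say for which outcomes, or that this would replace the ANOVA.

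**The concern.** Standard repeated-measures ANOVA needs a value at every occasion it includes, so a participant who misses one of them contributes nothing, including the values that were recorded. With frequent measurement over two years and one in five expected to leave, that is a costly choice.

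Two things are at stake. One is precision: data already collected are set aside. The other is bias: if the chance of being missing depends on earlier scores, and does so differently in the two arms, completers no longer give a fair comparison of the arms as randomised. A likelihood-based mixed model on the same data uses the partial records and stays valid when missingness depends only on what was observed.

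This matters for this trial because mechanisms of action are its stated secondary aim, and the Discussion makes the health-economic evaluation a critical focus.

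**Working it through.** **Inputs from the article.** Relapse rates 21.5% and 41.7%, uncorrected chi-squared test, 80% power, α = 0.05, 82 completers per group, 20% dropout, 102 recruited per group (204 in total); follow-up of two years; three-monthly measurement for most self-report measures.

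**Assumptions, not in the article.** Eight post-programme visits (24 months ÷ 3). A chance *m* of missing any one visit among those who have not dropped out, independent across visits, shown at 0%, 2%, 5% and 10%.

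**1. The plan's own figure.** n = [1.96·√(2p̄q̄) + 0.84·√(p₁q₁ + p₂q₂)]² ÷ (p₁ − p₂)², with p₁ = 0.215, p₂ = 0.417 and p̄ = 0.316. Two-sided and without continuity correction this gives 82 per group, as stated (power 0.800). Then 82 ÷ 0.80 = 102.5. The stated 102 is within rounding. This sizes the relapse comparison; no figure is given for the secondary outcomes.

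**2. Participants kept by a complete-case ANOVA.** Share = (1 − 0.20) × (1 − m)⁸.

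| m | share | of 204 |
|---|---|---|
| 0% | 0.800 | 163 |
| 2% | 0.681 | 139 |
| 5% | 0.531 | 108 |
| 10% | 0.344 | 70 |

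Only the first row rests on the article's figures alone: dropout by itself removes 204 − 163 = 41 people.

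For a measure with follow-ups at 12 and 24 months only, the 5% row becomes 0.80 × 0.95² = 0.722, or about 147 of 204.

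**3. Participants used by a mixed model on the same data.** Anyone with at least one post-baseline value contributes. If dropout is spread evenly over the eight visits (assumed), the share with none is Σⱼ (0.20/8)·mʲ⁻¹ + 0.80·m⁸, for j = 1 to 8. For m from 0% to 10% this leaves 198 to 199 of 204.

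Not all of the ANOVA's loss is recoverable at 24 months, because those who left have no value there. At m = 5%, however, 204 × 0.80 × 0.95 ≈ 155 people would have a 24-month value, against the 108 the ANOVA would use.

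**4. What the smaller number does to power.** For an illustrative standardised difference of 0.4 (assumed) and one comparison of two means, power = Φ(0.4·√(n/2) − 1.96), with n per group: 0.82 at 102, 0.73 at 82, 0.55 at 54 (the 5% row) and 0.39 at 35 (the 10% row). The mixed model is not the 102 case; it lies between the complete-case figure and that one.

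**5. Bias.** A simulation of 400 trials with 102 per arm assumed a fixed correlation over time, dropout depending on the previous score in the control arm only, and 5% intermittent missingness. About 55% had complete data.

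| true difference at last visit (SD) | completers: mean estimate (sampling SD) | likelihood model: mean estimate (sampling SD) |
|---|---|---|
| 0 | 0.075 (0.185) | −0.001 (0.153) |
| −0.4 | −0.313 (0.196) | −0.408 (0.153) |

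The completer estimate is off by 0.08 to 0.09 SD. The likelihood model is within 0.01 SD and more precise. The likelihood model was given the true covariance, which favours it somewhat.

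**The case against.** The best defence is that the article already deals with this. It promises imputation across its analyses and allows multilevel modelling, and a multilevel model for repeated measures is essentially what is asked for here. ANOVA on imputed data keeps every randomised participant. So a reader might infer that the secondary analysis is simply not ITT, or rests on complete cases alone, and the article does not support that. The explicit ITT sentence also sits under the primary-outcomes heading. What the defence does not reach is the main estimate: imputation is assigned to sensitivity analyses, and the multilevel model is conditional and tied to no outcome. It could as well be meant for clustering by site or therapy group.

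A second objection is that a condensed article leaves detail to the full protocol or SAP. That is right for how many occasions enter the ANOVA, whether sphericity is corrected, and whether baseline is an outcome level or a covariate. A reader might infer that sphericity is assumed and baseline treated as an outcome, but neither is in the text and neither is part of this point. The method itself, however, is stated and so is open to comment.

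A third objection is that the larger losses are assumed. This stands. The visit count and missed-visit rates are not in the article. Missed visits tend to cluster within people, which would leave more complete records than independence implies. The Retention section also describes active measures against missed assessments.

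Last, it is tempting to say that people who relapse miss visits, so that completers are the well. That is plausible, but nothing in the article documents it. Whether the arm contrast is biased, and in which direction, depends on how missingness works in each arm.

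**Conclusion.** The concern holds in a limited form. The main analysis named for the repeated secondary outcomes and for cost-utility is one that, in its standard form, sets aside participants with incomplete data. The provisions elsewhere in the article do not change which analysis is the main one.

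On the article's own dropout figure the loss is about 41 of 204 (163 kept). Anything larger, such as 108 of 204, depends on an assumed eight visits and an assumed independent 5% missed-visit rate, and is smaller for the annual measures. Loss of precision follows directly from the lost records. Bias is possible but conditional: it needs missingness that depends on earlier scores, and the 0.08 to 0.09 SD found above belongs to one assumed mechanism.

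Nothing here touches the relapse comparison, whose 82 per group reproduces.

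**What to change.** Under Secondary outcomes and mediation, replace repeated-measures ANOVA with a multilevel (mixed) model for repeated measures, fitted to all observed data, with participants analysed by randomised arm and with terms for arm, visit, arm-by-visit and the baseline value. Under Economic evaluation, do the same for the repeated AQoL comparison. State that this is the use of multilevel modelling the article already allows, so that it is no longer conditional for these outcomes.

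Keep imputation as the sensitivity analysis. The mixed model still leaves out the few people with no post-baseline value (about 5 or 6 of 204 in the working) and relies on missingness being explained by observed data, so a check on both remains useful. Covariance structure and further covariates can be left to the SAP.

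The cost is a change of wording and slightly more analysis work. No participants, visits or measures are added, and the primary analysis and sample size stay as they are.

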#### Economic evaluation

The incremental cost of MBCT is the cost of treatment less any savings in health service use. Results of incremental cost-effectiveness analysis will be subject to extensive probabilistic sensitivity analysis [66] using @Risk software, which allows the results to be presented as cost-effectiveness acceptability curves [67]. The cost-utility of MBCT + DRAM compared to DRAM alone will be compared using repeated-measures ANOVAs.

As recommended by Hollis and Campbell [68], sensitivity analyses will be undertaken across these analyses to examine the potential influence of the missing data using various forms of imputation. Where appropriate, given the design of the study, multilevel modelling will be employed [69].

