#### Health Economics

Kuyken et al [14] examined the cost effectiveness of MBCT compared to m-ADM. Although not conclusive, this work suggested that MBCT was more expensive than m-ADM over the first 12 months with costs then converging and MBCT becoming cheaper over the subsequent 3 months. The authors speculated that the cost-effectiveness of MBCT may increase over time and recommended examining the cost-effectiveness of MBCT over longer follow-up periods. More generally, later phase translational research questions would be served by a health economics study and analysis taking into account local service context, real-world conditions including combined treatment with anti-depressant medication and multiple economic perspectives.

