#### Economic analysis

Service utilisation by self-report is assessed with instrumentation used in the most recent (2007) Australian National Survey of Mental Health and Wellbeing. This instrument was used in the first national survey in 1997, but has been updated to take into account identified deficiencies in the earlier instrument [57]. It includes some elements of the service utilisation section of the WHO CIDI [44]. It also contains questions relating to levels of perceived need for mental health care and so provides a consumer appraisal of the relative adequacy of overall service provision [58-60]. As the instrument was prepared drawing on a national expert group with support of the Australian Bureau of Statistics, this likely represents the best developed instrument for collection of service utilisation data in Australia.

In order to estimate costs associated with lost productivity, every 3 months participants in the study are asked to record the number of days they had been absent from their usual work or occupation due to illness or disability. Also collected is their account of how many of these days were due to depression or related problems with their mental health. Employment status and, for those working, current occupational status are rated using the *Australian and New Zealand Standard Classification of Occupations *[61]. The AQoL will also be used to assess the cost-utility of MBCT in terms of quality-adjusted life years (QALYs).

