The need to balance competing questions of interest is an important consideration in the design of RCTs. For example, the recommended comparator for a health economic analysis is a TAU control [70], while an active alternative treatment is likely to provide the most information for studies investigating mechanisms of action [e.g., [71]]. As an effectiveness trial, a health economic analysis is an important aspect of the present study so favouring the selection of a TAU control in the design. However, we had the additional need to control for the potential bias of resentful demoralization and so the self-monitoring intervention DRAM was introduced as an addition to TAU. This is likely to mean that episodes of depression are picked up and treated earlier than would be the case without such monitoring and possibly lead to a relative weakening of the between-group effects for standard symptom measures [72]. Nevertheless, we predict that the impetus to access treatment prompted by DRAM will, if anything, increase between-group differences in the health economic evaluation and so this will form a critical focus for examination. In addition, with respect to relapse outcomes, substantial reliance will be placed on measures relating to time to clinical intervention.

Historically, health care systems have been heavily oriented to the treatment of illness, rather than to its prevention, resulting in costs that have been described as spiralling out of control [73]. The argument has been put forward that where preventative and especially "low tech" interventions such as mindfulness-based interventions are available, priority should be given to exploring how best to implement them for greatest impact [73]. The results of this trial, including an examination of clinical, functional and health economic outcomes, will be used to assess the role that this treatment approach may have in recommendations for treatment of depression in Australia and elsewhere. We expect that the findings from this research will consolidate the evidence-base to guide the decision to fund MBCT and to seek to promote its availability to those who have experienced at least three episodes of depression.

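### Cost-utility is assigned to repeated-measures ANOVA, which cannot give an incremental cost per QALY or its joint uncertainty; the planned acceptability-curve framework should cover it instead

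*Protocol article*

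**What the plan says.** All references are to the protocol article.

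- **Economic evaluation** (Statistical analysis) defines cost: "The incremental cost of MBCT is the cost of treatment less any savings in health service use". It then says: "Results of incremental cost-effectiveness analysis will be subject to extensive probabilistic sensitivity analysis", to be presented as acceptability curves. The effect measure of that analysis is not named. The next sentence deals with cost-utility separately: "The cost-utility of MBCT + DRAM compared to DRAM alone will be compared using repeated-measures ANOVAs".
- **Economic analysis** (Measures) names the effect measure for cost-utility: "The AQoL will also be used to assess the cost-utility of MBCT in terms of quality-adjusted life years (QALYs". It also collects absence data for a stated costing purpose: "In order to estimate costs associated with lost productivity, every 3 months participants in the study are asked to record the number of days" lost through illness or disability.
- **Assessments** (Procedure) schedules service utilisation at 12 and 24 months after the MBCT programme ends. The AQoL is not in that list, so it falls among the remaining self-report measures, given every 3 months.
- **Aims of trial** places health economics beside clinical impact in the main aim. The **Discussion** expects the self-monitoring component to "increase between-group differences in the health economic evaluation and so this will form a critical focus for examination".

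**The concern.** Cost-utility analysis asks how much extra cost, if any, buys one extra QALY, and how certain that answer is. It needs two between-arm differences, in mean total cost and in mean QALYs, together with their joint distribution. Repeated-measures ANOVA handles one repeatedly measured variable and tests group and group-by-time effects on its mean. The article names this method, so it is a stated choice and not a detail left to a fuller plan.

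The Discussion expects the findings to inform a decision on funding MBCT. Such a decision needs the quantity that the named method does not produce. If the sentence stands, the analyst must either report something that is not a cost-utility result or choose another method after seeing the data.

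A lesser matter concerns the cost side. Absence days are gathered expressly to cost lost productivity, but the one definition of incremental cost has no productivity term.

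**Working it through.** **The plan's own figure.** No economic figure is stated. The only sample-size figure is for relapse (Power analysis): 21.5% against 41.7%, 80% power, α = 0.05, uncorrected chi-squared. Taken as two-sided, with mean proportion 0.316:

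n = [1.960·√(2·0.316·0.684) + 0.842·√(0.215·0.785 + 0.417·0.583)]² / 0.202² = (1.289 + 0.540)² / 0.0408 ≈ 82 per group.

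This matches the stated 82. The point does not depend on it; 82 serves below only as a convenient number per arm.

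**What an ANOVA could be run on.**

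1. *AQoL utilities at each visit.* With equally spaced visits, the group effect is close to an average utility difference. It contains no cost.
2. *Costs.* This contains no QALYs.
3. *A cost-to-utility ratio at each visit.* Service use is recorded at 12 and 24 months and the AQoL every 3 months, so no such series exists. A mean of individual ratios would in any case differ from the ratio of the two mean differences.

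None of the three gives an incremental cost per QALY or a net benefit.

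**Illustration. Every input except 82 is an assumption; none comes from the documents.** QALY gain 0.06 with SD 0.25; extra cost 1,200 with SD 5,000; willingness to pay 50,000 per QALY; √(2/82) = 0.1562.

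- Between-arm test of QALYs: z = 0.06 / (0.25 × 0.1562) = 1.54. Cost does not enter.
- Net benefit: 50,000 × 0.06 − 1,200 = 1,800.
- Its variance per person, with cost-QALY correlation ρ: 12,500² + 5,000² − 2ρ(12,500)(5,000) = 181.25 million − 125 million × ρ.
- Its standard error is the square root of that variance times 0.1562:

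| ρ | SE of net benefit | z | Probability cost-effective |
|---|---|---|---|
| −0.5 | 2,438 | 0.74 | 0.77 |
| 0 | 2,103 | 0.86 | 0.80 |
| 0.5 | 1,702 | 1.06 | 0.85 |

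The same QALY test result goes with each of these rows. Neither a separate ANOVA of utilities nor one of costs can tell them apart.

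**Productivity, same assumed inputs.** Cost per QALY = (1,200 − S) / 0.06, where S is the productivity saving per person:

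- S = 0: 20,000
- S = 500: 11,667
- S = 1,000: 3,333
- S = 2,000: net cost −800, so MBCT is both cheaper and more effective

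Whether productivity is counted can therefore change the conclusion. Whether it would do so in this trial cannot be known from the documents.

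**The case against.** The strongest reply is that the plan already has the pieces: an incremental analysis, a probabilistic method with acceptability curves, and QALYs as an outcome. On that reading the ANOVA sentence is loose wording for comparing AQoL scores between arms. This is plausible, and it rules out two stronger conclusions that a reader might draw:

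- *That the economic evaluation has no method for uncertainty.* It has one. The fault is that cost-utility is not put through it.
- *That the trial cannot answer the cost-utility question.* The AQoL, service-use and absence data are all collected. Only the named analysis is unsuitable.

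The reply does not rescue the sentence. If the framework was meant to cover QALYs, the sentence is wrong; if it was not, the QALY analysis has no suitable estimator.

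Three further inferences are not supported:

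- *That anyone with a missed visit is lost.* The same section plans imputation sensitivity analyses and, where appropriate, multilevel modelling.
- *That chance baseline imbalance in AQoL would swamp the QALY effect.* That presumes an unadjusted area-under-the-curve analysis, which the plan never states, and utility figures that it does not give.
- *That the cost definition is invalid or prejudges direction.* Treatment cost less service savings is acceptable from a health-sector perspective, and savings can turn out zero or negative. The Background phrase "real-world conditions including combined treatment with anti-depressant medication and multiple economic perspectives" describes what later-phase research would benefit from; it is not a commitment of this trial.

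What remains of the productivity point is narrower: data are collected to be costed, no perspective is named for the one cost definition, and no stated analysis uses them.

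**Conclusion.** The point holds on the text. Repeated-measures ANOVA is the wrong method for the cost-utility comparison, and the incremental framework in the sentence before is not extended to it. This affects an aim that the article ranks with clinical impact, so it should be corrected before the economic data are analysed.

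No size can be computed from the documents, which state no costs, utilities or standard deviations. The illustration shows only that the ANOVA result is blind to cost and to the cost-QALY correlation; its figures rest on the listed assumptions and predict nothing about this trial. The omission of productivity from the cost definition is secondary and calls for clarification.

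A reader might infer that the trial's main conclusion is at risk. It is not: relapse is the primary outcome, and its analysis and sample size do not depend on any of this.

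**What to change.** Replace the cost-utility sentence so that it states:

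1. For each participant, 2-year QALYs are the area under the 3-monthly AQoL utility curve, and total cost is summed over the same period. The QALY comparison is adjusted for baseline AQoL.
2. The incremental cost per QALY, or the incremental net benefit, is estimated with joint uncertainty, for example by bootstrapping each participant's cost and QALY as a pair.
3. The result is shown on the acceptability curves already planned.

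Repeated-measures ANOVA can stay for AQoL scores as a secondary outcome.

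As a smaller change, define incremental cost as the difference between arms in mean total cost. Report it from a health-sector perspective and again with lost productivity included.

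The cost is a revised paragraph and a little more analysis work. No new data are needed, and the relapse analysis and sample size stay as they are.
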